## Abstract

**Background:**

Urban South-Asian's are predisposed to early onset of type 2 diabetes mellitus (T2DM) and cardiovascular disease (CVD). There is an urgent need for country specific primary prevention strategies to address the growing burden of cardio-metabolic disease in this population. The aim of this clinical trial is to evaluate whether intensive (3-monthly) lifestyle modification advice is superior to a less-intensive (12 monthly; control group) lifestyle modification advice on a primary composite cardio-metabolic end point in 'at risk' urban subjects aged between 5-40 years.

**Methods/Design:**

This is an open randomised controlled parallel group clinical trial performed at a single centre in Colombo, Sri-Lanka. A cluster sampling strategy was used to select a large representative sample of subjects aged between 5-40 years at high risk of T2DM and CVD for the intervention study. We have screened 23,298 (males 47% females 53%) healthy subjects for four risk factors: obesity, elevated waist circumference, family history of diabetes and physical inactivity, using a questionnaire and anthropometry. Those with two or more risk-factors were recruited to the intervention trial. We aim to recruit 4600 subjects for the intervention trial. The primary composite cardio-metabolic end point is; new onset T2DM, impaired glucose tolerance, impaired fasting glycaemia, new onset hypertension and albuminuria, following 5 years of intervention. The effect of the intervention on pre-specified secondary endpoints will also be evaluated. The study will be conducted according to good clinical and ethical practice, data analysis and reporting guidelines.

**Discussion:**

DIABRISK-SL is a large population based trial to evaluate the prevalence of diabetes, pre-diabetes and cardio-metabolic risk factors among young urban Sri-Lankans and the effect of a primary prevention strategy on cardio-metabolic disease end points. This work will enable country specific and regional cardio-metabolic risk scores to be derived. Further if the proposed intervention is successful the results of this study can be translated and implemented as a low-cost primary prevention tool in Sri-Lanka and other low/middle income developing countries.

**Trial registration:**

The trial is registered with the World Health Organisation and Sri-Lanka clinical trial registry number SLCTR/2008/003

## Background

Type 2 Diabetes Mellitus (T2DM) and associated cardiovascular complications pose a major health-care burden worldwide and present a significant challenge to patients, health-care systems, and national economies [1]. Nearly two thirds of the estimated 285 million people with diabetes (predominantly T2DM) live in low and middle income countries [1,2]. Recent data indicates that South Asia is one of the major sites of this epidemic of T2DM with a projected 72% increase in the number of subjects with T2DM in the next 20 years [1]. In parallel there is an epidemic of pre-diabetes [impaired glucose tolerance (IGT) and impaired fasting glycaemia (IFG)], with prevalence rates between 10-15% reported in South Asian adult populations [1].

T2DM and IGT are associated with a significantly increased risk of cardiovascular disease (CVD) with South Asian's particularly predisposed to early onset of T2DM and CVD [1]. In South Asia almost a third of T2DM cases will be in those aged below 45 years [1]. Both CVD and T2DM may share a common pathogenesis and indeed retain many common risk factors/features [1].

Sri Lanka is a middle income country in Asia with a population of 20 million. Nearly 40% of Sri Lankans are aged below 40 years and 25% are aged below 18 years [3]. There has been a rapid urbanisation in recent decades with an estimated 30% of the population now living in urban areas [3]. The most recent national study in subjects aged over 20 years indicated a population prevalence of dysglycaemia (defined as T2DM or IGT or IFG) of 20% which rose to 30% in urban areas [4]. Physical inactivity, raised body mass index (BMI) and central obesity along with urban living were strongly associated with the increased risk of dysglycaemia.

The majority of lifestyle modification (LSM) intervention studies/programmes on preventing T2DM have been done in older pre-diabetic subjects with mean ages between 45-50 years [5-7]. A recent meta-analysis suggested that in subjects with IGT, the number needed to treat to prevent one case of T2DM was 10.8 with anti-diabetic drugs as compared to 6.4 with LSM [8]. Furthermore long term 'legacy' benefits of LSM which can last up to 14 years following the cessation of LSM have been reported [9,10].

To date there is limited information on the prevalence of T2DM and cardio-metabolic risk factors in young urban populations from Sri-Lanka or other similar South-Asian countries. Moreover the effect of a LSM programme on cardio-metabolic disease end-points has not been hitherto evaluated in this unique population.

### General objective

The objective of the trial is to test the hypotheses that intensive (3 monthly) LSM advice will be superior to less intensive (12 monthly) LSM advice in preventing cardio-metabolic disease in 'at risk' young urban Sri Lankan subjects.

### Primary objective/end-point

The primary objective of the trial is to determine whether intensive (3 monthly) LSM advice will be superior to less intensive (12 monthly) LSM advice in reducing the primary composite cardio-metabolic end point of new onset T2DM, impaired glucose tolerance, impaired fasting glycaemia, new onset hypertension and albuminuria at 5 years.

### Secondary objective/endpoints

Secondary end-points include; the individuals components of the primary composite end-point, incidence of metabolic syndrome as defined by the International Diabetes Federation (IDF) [11,12], incidence of pre-hypertension as defined by Joint National Committee on Prevention, Detection, Evaluation, and the Treatment of High Blood Pressure (JNC-7) [13], regression of IGT and IFG, [IGT and IFG will be defined as per World Health Organisation (WHO) and American Diabetes Association criteria [14,15]] and changes in: weight, BMI, waist circumference (WC), fasting triglycerides, fasting high density lipoprotein (HDL) and low density lipoprotein (LDL) cholesterol, serum creatinine and estimated glomerular filtration rate (GFR), physical activity as measured by the International physical activity questionnaire (IPAQ)[16], depression, as measured by PHQ-9 questionnaire, [17], and psychological stress, as measured by perceived stress scale [18]. Adherence to diet and physical activity will be self-reported based on weekly pattern and evaluated at study visits. The effects of baseline risk factors on the development of end-points will also be evaluated in analyses.

Quality of life measures will be evaluated using a validated short version of the multidimensional WHO Quality of Life questionnaire (WHOQOL-Bref) [19]. Health economic analyses by the Public Health Department University of Colombo with advice and guidance from Division of Social Care and Policy at King's College London is an area we plan to develop utilising models described in recent studies [20].

## Methods/Design

### Study design

DIABRISK-SL is an open randomised controlled parallel group clinical trial evaluating the effect of intensive (3-monthly; study group) *vs*. less-intensive (12-monthly; control group) LSM advice on a primary composite cardio-metabolic end-point (new onset T2DM, IGT, hypertension, and albuminuria) in 'at-risk' young urban subjects aged between 5-40 years. The two arms of the study have 1:1 allocation ratio and follow up is over 5 years. Figure 1 details the trial flow chart.

**Figure 1 F1:**
[figure not shown]
**Trial flow chart**. Figure 1 describes trial flow chart from screening to randomisation and end point evaluation at 5 years.

### Ethics and Trial Registration

The study is funded by IDF BRIDGES, an IDF project supported by an educational grant from Eli Lilly Diabetes and a grant award from the Diabetes Association of Sri Lanka (DASL). The study protocol is approved by Ethical Review Committee of Sri Lanka Medical Association (ERC 07-010). The trial is registered at Sri Lanka Clinical Trials Registry (Clinical Trial Registration Number SLCTR/2008/003), available online at: http://apps.who.int/trialsearch/Trial.aspx?TrialID=SLCTR/2008/003.

### Study population and recruitment

We screened a population representative of the general population of Colombo District, the most populous urban district in Sri-Lanka, aged between 5 to 40 years to identify the prevalence of four risk-factors namely first degree family history (FH) of T2DM, physical inactivity, raised BMI and raised WC. The sampling strategy was designed to provide a sample that was representative of the age and sex distribution of the general population aged between 5-40 years in the Colombo district [3]. A list of schools, workplaces, universities and community organisations was made that were representative of the organizations and population aged between 5 to 40 years obtained from the most recent national census results. This list comprised of 65 organisations and each of these organizations was individually approached and eligible participants were invited to take part in the screening study. The screening survey took place between 1^st ^January 2008 and 30^th ^June 2009. The age and sex distribution of the screened population was regularly compared with the distribution of the reference population to ensure that the screened population was representative of the distribution of the general population aged between 5 and 40 years in the Colombo district. More than 95% of subjects and institutions approached agreed to participate. Subjects with a known history of T2DM, CVD, hypertension or diabetes and pregnant women were excluded from the initial sample. Subjects on lipid lowering drugs or anti-diabetic or anti-hypertensive drugs were also excluded.

Subjects with any active communicable or non-communicable chronic disease (NCD) such as cancer, asthma or other forms of chronic lung disease, depression, and tuberculosis were also excluded. A screening questionnaire (see additional files 1) was used to determine first degree family history of T2DM and the physical activity of the individual participants. Further information regarding socio-demographic factors was also collected.

The screening study aimed to identify four risk-factors: physical inactivity (<30 minutes continuous exercise for <3 days/week), raised WC (central obesity) defined as WC in subjects between 5-17 yrs ≥91^th ^percentile, 18-40 yrs: females ≥80 cm and males ≥90 cm, first degree FH of T2DM and raised BMI defined in subjects aged 5-18 yrs of a BMI value greater than internationally standardized age and sex specific percentile cutoffs and between 18-40 yrs as BMI ≥23 kg/m^2 ^[21,22]. These four factors were chosen on the basis of a pilot study that identified these risk-factors as being highly prevalent in 1239 subjects aged below 40 years with a new diagnosis of T2DM who attended the National Diabetes Centre in Colombo between 2005-2007 and are supported by recent data from comparable South Asian and Sri Lankan populations [1,4,22,23].

### Inclusion Criteria for primary prevention intervention trial

Subjects aged 5-40 years with two or more risk factors for cardio-metabolic disease. The risk factors for selection included two or more of the following;

• ***First degree FH of T2DM***

• ***Physical inactivity***

• ***Raised BMI***

• ***Raised WC***

### Exclusion Criteria

#### During screening

• Subjects with no or one identifiable risk factor

• Subjects with diagnosed end-points (T2DM, CVD, hypertension and renal disease)

• Subjects on any form of medication used for the treatment of diabetes, hypertension, renal disease or dyslipidaemia

• Any active communicable or NCD such as cancer, asthma or other forms of chronic lung disease, depression, tuberculosis.

• Pregnant women

#### During the primary prevention intervention trial

• Subjects who reach one or more of the following cardio-metabolic end-points; T2DM, CVD, hypertension, and albuminuria.

• Subjects initiated on any form of medication used for the treatment of diabetes, hypertension, renal disease or dyslipidaemia by their family physician or other medical physician.

• Pregnancy at any stage of the study

### Randomisation

Subjects who satisfy the selection criteria will be randomised into two intervention group using a computer generated randomisation schedule/sequence (SPSS 10.0) prepared by an independent party (Department of Statistics and Public Health Colombo University). Randomisation was performed sequentially using a SPSS programme function which enables this process and is supervised by an independent statistician from the Department of Statistics and Public Health at Colombo University, Sri Lanka.

#### Procedures

The following procedures and measurements will be performed at baseline prior to randomisation to one of the two groups.

Height is measured using a portable stadiometer (Seca France) and taken to the closest 0.1 cm, and weight is measured without footwear in light clothing to the nearest 100 g with an electronic weighing scale (Seca France). Both instruments are calibrated weekly. BMI is calculated as weight in kilograms divided by height squared in meters. WC is measured using a graduated measuring tape (Seca France), calibrated weekly, with a locking device to the nearest 0.1 cm. WC is taken at the mid-point between the iliac crest and the last rib in expiration. Blood pressure is measured by automatic oscillometry from the non-dominant arm after 5 minutes rest with the mean of two measurements recorded (Riester Ri-Champion Riester, Jungingen, Germany). WHO approved growth charts for male and female children will be used [24].

Fasting plasma glucose and a standard 2-hour 75 g oral glucose tolerance test (OGTT) is performed in adults and glucose solution 1.75 g/kg body weight, to a maximal dose of 75 g is given to those below 16 years following a 12-hour fast as per WHO guidelines [14]. Plasma Glucose, total cholesterol, high density density lipoprotein (HDL), low density lipoprotein (LDL), triglycerides and serum creatinine will be measured by enzymatic colorimetry (Vitros MS 250, Ortho Clinical Diagnostics, Johnson and Johnson, Co, Rochester USA). Fasting plasma insulin will be measured using radioimmunoassay (Immulite, Siemens, Surrey, UK), which has a sensitivity of 4 μU/ml (<24 pmol/l) and intra and interassay coefficients of variation <8%. Insulin resistance will be calculated using the homeostasis model assessment of insulin resistance (HOMA-IR) [25]. Urine albumin to creatinine ratio will be measured by immunoturbidemtry (Vitros 5,1 FS Chemistry System, Ortho-Clinical Diagnostics, Johnson and Johnson Company, Hampshire, United Kingdom) from an early morning urine sample. In subjects below 18 years the Schwartz equation will be used to estimate glomerular filtration rate (GFR) from serum creatinine values [26] and in subjects above 18 years the Modification of Diet in Renal Disease (MDRD) Study equation will be used to estimate GFR [27].

### Intervention and goals

Intensive LSM group: The main goals of the intensive group delivered three monthly on an individual basis are:

Dietary advice and support: individualised advice is given on the need to have a well balanced food intake and to maintain appropriate body weight in those with normal BMI and WC. In subjects with a raised (age and gender appropriate) BMI and WC a goal of >5% weight loss is set concordant to targets in recent studies [5-8]. Dietary advice on avoiding a high intake of food containing simple sugars, refined carbohydrates and high saturated fats (total fat intake <20 g/day) and advice to increase intake of healthy natural foods which are fibre-rich-whole grains, legumes, vegetables and fruits is given. A list of refined foods to be avoided is provided. Subjects are advised on the importance of regular meals and to avoid delaying or missing meals.

Exercise; Subjects with physical inactivity at baseline are advised to increase physical activity to at least 30 minutes of continuous exercise a day for more than 5 days of the week. Individualised exercise advice is given depending on the needs and facilities available to the subject. Children are advised on need to play at least for 1 hour every day. All subjects are advised to minimise sedentary activity such as watching television. For children, the LSM advice will be given to the parent and the child jointly. To ensure that the intervention does not hamper normal growth, assessment of the child's growth (height and weight) will be performed at each visit and these measures compared to the previous values on the child's growth chart; and if there is any medical and or parental concerns regarding growth, the child will be referred to a paediatrician for further evaluation and assessment.

The dietary and exercise goals are comparable to those set in the Indian Diabetes Prevention Programme (IDPP) [6]. All subjects have a three monthly telephone contact to assess progress and reiterate goals. The total number of one to one contacts is 4 per year. The basis of LSM advice is made on the transtheoretical model of behaviour change [28] which postulates that individuals are at different stages of readiness to adopt a new behaviour and that individuals are required to progress through various 'stages of change'. Evidence suggests that providing individualised interventions tailored to a subject's stage of behaviour change i.e. stage matched, as done in this study, are more effective than providing the same intervention to all subjects [29].

Control group: Less intensive (annual) lifestyle advice: Identical dietary and exercise advice as outlined above are given to all subjects in the control group; however this is done on a 12 monthly basis. The goals and targets set for diet and exercise are identical to those in the intensive group but these are evaluated and reinforced annually in one individualised face to face contact session with an educator.

### Statistical methods and power calculation

Approximately 2300 subjects with ≥2 risk-factors are required in each group (4600 subjects in total) to detect a 25% relative risk reduction at 5 years on the primary composite cardio-metabolic end-point of new onset T2DM, IGT, IFG, hypertension, albuminuria, renal and CVD events with intensive LSM. The study is powered at the 90% level with a type-1 error of 0.05 (2 sided) assuming a 15% incidence of the primary end-point in the control group and including allowance for 25% drop-out of subjects. The proposed 25% relative risk reduction of the composite outcome is derived from the effects of intensive LSM programme reducing the relative risk of new onset T2DM in South Asian IGT patients [1,6].

There will be a pre-specified interim analysis of the composite primary and secondary endpoints at 2 years, as requested by one of the funding bodies (IDF BRIDGES). This analysis will be performed by an independent statistician and the trial investigators will remain blinded to the full data analyses and interim results. All data related to interim analysis will directly forwarded to funding body by the independent statistician and will be strictly confidential and not for public dissemination/publication.

Descriptive statistics will be used for the analysis of demographic and clinical features of the cohort. Two-sided t-tests and chi-square (χ^2^) tests will be used to analyze the comparison between the groups at baseline and during follow-up. Survival curves will be calculated to estimate the cumulative incidence of the composite primary end-point and secondary end-points. The difference between the groups in the primary end-point will be tested by means of the two-sided log-rank test. All analyses of end-points are based on the intention-to-treat principle. Analyses will be performed using STATA software version 10 (Stata Corp, College Station, TX, USA).

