### Definition of primary cardio-metabolic end-points

▪ **New onset T2DM **as indicated by either a fasting plasma glucose of ≥7.0 mmol/l and/or a 2-hr plasma glucose concentration of ≥11.1 mmol/l during an annual follow-up confirmed by repeat 75 g OGTT as per World Health Organization (WHO) criteria [14] or initiation anti-diabetic treatment by the subject's family physician following confirmatory tests.

▪ **New onset IGT **is defined as a plasma fasting glucose <7.0 mmol/l and 2-h glucose 7.8-11.0 mmol/l and IFG as fasting plasma glucose between 6.1 to.9 mmol/l or 5.6 to 6.9 mmol/l [14,15].

▪ **New onset hypertension **is defined as mean brachial blood pressure from 2 readings taken following 5 minutes rest ≥140/90 mmHg or initiation of anti-hypertensive treatment commenced by the subject's family physician as per JNC-7 criteria [13]. In those below 18 years hypertension is defined as blood pressure that is, on repeated measurement, at the 95^th ^percentile or greater adjusted for age, height, and sex [13].

▪ **New onset albuminuria is defined as **urine albumin/creatinine ratio ≥2.5 mg/mmol in males and ≥3.5 mg/mmol in females from early morning sample confirmed on one repeat test.

▪ **New onset renal impairment is **defined as estimated GFR <60 ml/min or doubling of serum creatinine from baseline.

▪ **CVD events **are defined as fatal and not fatal events of Myocardial infarction (MI): Congestive heart failure (CHF): death due to clinical, radiological or post-mortem evidence of CHF, Stroke, vascular revascularisitation and admission for unstable angina.

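### The primary composite is listed with four, five and seven components and IFG has two lower limits, so the primary test has no single target and the power statement belongs to a list other than the stated objective's

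*Protocol article*

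**What the plan says.** Three lists in the protocol article are each called the primary composite.

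- **Five components.** The section Primary objective/end-point gives the "primary composite cardio-metabolic end point of new onset T2DM, impaired glucose tolerance, impaired fasting glycaemia, new onset hypertension and albuminuria at 5 years". The abstract gives the same five.
- **Four components.** Study design gives "new onset T2DM, IGT, hypertension, and albuminuria". IFG is absent.
- **Seven components.** Statistical methods and power calculation gives the "primary composite cardio-metabolic end-point of new onset T2DM, IGT, IFG, hypertension, albuminuria, renal and CVD events with intensive LSM". Consistent with this, the section headed "Definition of primary cardio-metabolic end-points" also defines CVD events and new-onset renal impairment, the latter "defined as estimated GFR <60 ml/min or doubling of serum creatinine from baseline".

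The definitions section gives "IFG as fasting plasma glucose between 6.1 to.9 mmol/l or 5.6 to 6.9 mmol/l". The upper limit of the first range is garbled in the text at hand and is not part of this point. Secondary objective/endpoints says "IGT and IFG will be defined as per World Health Organisation (WHO) and American Diabetes Association criteria", so it names two sources and chooses neither.

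The 15% control incidence, 25% relative risk reduction, 90% power and 4600 subjects appear together only in the power section, next to the seven-component list. The same section plans a two-sided log-rank test of the primary end-point without saying which list it means.

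**The concern.** A confirmatory trial needs one primary endpoint, fixed in advance. Here someone programming the primary analysis could follow any of three sections and obtain a different set of events. The secondary endpoints inherit the problem, because they include the individual components of the primary composite. So does the 2-year interim analysis, which covers the same composite.

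Two things are at stake. First, the trial is open. If the definition is still unsettled when outcomes by arm are known, it can be chosen with that knowledge, and the 5% type I error no longer protects the primary claim. Second, the power statement describes the seven-component endpoint, whereas the objective to be tested names five components.

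**Working it through.** **1. Counting the possible endpoints**

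| Component list | IFG from 6.1 | IFG from 5.6 | Distinct endpoints |
|---|---|---|---|
| Four (Study design) | not applicable | not applicable | 1 |
| Five (abstract, Primary objective) | yes | yes | 2 |
| Seven (power section, definitions) | yes | yes | 2 |

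Total: 1 + 2 + 2 = 5. If the word joining the two IFG ranges is read as a union, the range is 5.6 to 6.9 mmol/l. That is the second column again and adds no further endpoint.

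**2. Reproducing the plan's sample size**

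Inputs, all from Statistical methods and power calculation: control incidence p1 = 0.15; relative risk reduction 25%, so p2 = 0.15 × 0.75 = 0.1125; two-sided alpha 0.05 (z = 1.960); power 90% (z = 1.282); drop-out 25%.

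Formula, with p̄ = 0.13125:

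n = [1.960 × √(2p̄(1 − p̄)) + 1.282 × √(p1(1 − p1) + p2(1 − p2))]² / (p1 − p2)²

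- First term: 1.960 × √0.22805 = 0.936
- Second term: 1.282 × √0.22734 = 0.611
- n = (0.936 + 0.611)² / 0.0375² = 2.393 / 0.001406, which gives 1702 per group
- After drop-out: 1702 / 0.75, which gives 2270 per group

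With continuity correction the result is 1755, or 2340 after drop-out. A log-rank calculation uses the hazard ratio implied by these proportions, ln(0.8875)/ln(0.85) = 0.734. It gives 2242 (Schoenfeld) or 2276 (Freedman) after drop-out. The stated figure of about 2300 is reproduced.

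**3. What follows if the list changes**

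Every event of the four- or five-component composite is also an event of the seven-component composite when the IFG range is the same. Incidence on a shorter list therefore cannot exceed incidence on the longer one. At a fixed relative risk reduction and fixed n, lower incidence means lower power. If 15% is right for seven components, the shorter lists have at most the stated power.

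This ordering needs the IFG range held fixed. The article does not say which range the 15% assumes. Five components with the wider range cannot be ranked against seven with the narrower one.

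**4. Illustration of size**

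Evaluable per group: 2300 × 0.75 = 1725.

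Power = Φ{[(p1 − p2)√n − 1.960 × √(2p̄(1 − p̄))] / √(p1(1 − p1) + p2(1 − p2))}, with p2 = 0.75 × p1.

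| Control incidence | Source | Power | Per group for 90%, with drop-out |
|---|---|---|---|
| 15% | stated | 90.4% | 2270 |
| 14% | assumed | 88.0% | 2456 |
| 12% | assumed | 82.0% | 2924 |
| 10% | assumed | 73.9% | 3578 |

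Only the 15% row rests on the article. The other rows show sensitivity and are not estimates of what happens when a component is dropped.

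**5. Where renal and CVD events stand under the five-component list**

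- Secondary objective/endpoints names neither CVD events nor new-onset renal impairment, only changes in creatinine and estimated GFR.
- The exclusion criteria that apply during the intervention trial list CVD among the end-points that take a subject out.
- The independent board is to adjudicate CVD events.

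Under five components, then, a CVD event would be adjudicated and would remove the subject, but would have no stated role in the analysis. The during-trial exclusion list (T2DM, CVD, hypertension, albuminuria) is a removal rule and not a fourth definition of the composite, but it matches none of the three lists.

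**The case against.** Much can be said for a milder reading. IFG appears in the abstract, the objective, the power section and the definitions; its absence from one parenthesis in Study design may be a slip. Renal and CVD events may be rare at ages 5 to 40, in which case the mismatch of five against seven components would move power little: a fall from 15% to 14% costs about two percentage points. The investigators are to stay blinded to the interim results, which limits data-driven choice at 2 years. The five endpoints are nested, so their results would be strongly correlated. An analysis plan may also settle the matter.

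Most of this stands as a limit on size, but it does not remove the conflict. Even with the four-component list set aside as a slip, five against seven components remains, between the formal objective on one side and the power statement and definitions on the other. The two IFG limits also remain. Blinding at the interim does not cover the final analysis, and the statistician running the interim needs one definition too. Nor is this detail left to a fuller document: the article specifies the endpoint and does so inconsistently.

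A reader might go further and infer any of the following, which the documents do not support:

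- **The sample size is miscalculated.** It is reproduced from its own inputs.
- **Power is known to be seriously short.** No component incidences are given, so no actual loss can be derived.
- **Type I error is already inflated, or someone intends to choose the endpoint late.** The text shows neither. The error rate is at risk only if the definition is chosen after outcomes by arm are seen.
- **The five-component list or the 6.1 limit is plainly the intended one.** The power calculation, the definitions and the CVD adjudication point to seven components, and both sources of IFG criteria are named.

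**Conclusion.** Wrong as written: an internal inconsistency in the primary endpoint that must be resolved. Three component lists and two IFG limits allow five distinct primary endpoints, and the log-rank test has no single target. The stated 90% power and 4600 subjects hold for 15% incidence and a 25% relative risk reduction, which the article attaches to seven components while its objective names five.

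The direction of the effect on power follows by logic, given the same IFG range and the same relative risk reduction: the stated level or lower for the shorter lists. Its size cannot be derived. The figures from 88% down to 74% rest on assumed incidences of 14% to 10%. The type I error point is conditional: nothing in the article prevents the definition from being chosen after the data are seen, and at the final analysis of an open trial that leaves the 5% level unprotected.

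**What to change.** Before anyone involved in the decision has seen outcome data by arm, the sponsor should:

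1. State one component list and one IFG range for the primary analysis, and use them in the abstract, Primary objective/end-point, Study design, Statistical methods and power calculation, and the definitions section. Which list and range to adopt is for the sponsor to justify; any one consistent choice removes the conflict.
2. Report the other IFG range as a labelled sensitivity analysis.
3. Tie the 15% incidence, the 25% relative risk reduction and the power to that list and range. If the expected incidence changes, restate the power.
4. Reconcile the role of renal and CVD events with the secondary endpoints, the during-trial exclusion criteria and the board's adjudication task, so that an event that removes a subject does not lack a stated role in the analysis.

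The cost is a dated amendment and a stated power that may be less favourable. The date matters: screening ended in June 2009 and the article already describes randomisation in the past tense, so the amendment should record that the choice was made without sight of outcomes by arm.
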